## Study management

3

The Data Monitoring Committee (DMC) will consist of at least two members from the Ethics Committee of Inner Mongolia Maternal and Child Health Hospital, who have no conflict of interest with the study. The committee will be responsible for conducting regular monitoring and review of the study, reporting the findings to the Ethics Committee to ensure the process is independent from the principal investigators. If the DMC identifies any deviations from the approved study protocol or unauthorized changes during the monitoring process, the committee has the authority to suspend or terminate the study. The hospital’s Ethics Committee will conduct a review every six months to assess progress and ensure adherence to the established protocol. Prior to the start of the trial, the principal investigator will meet with the research team weekly to ensure that all procedures comply with the protocol standards. During the data collection phase of the trial, the research team will hold monthly meetings, and the principal investigator and trial manager will maintain daily communication to ensure protocol adherence.

During the study, the research team must report any Serious Adverse Events (SAEs) or Adverse Events (AEs) to the Ethics Committee quickly. If a participant has any SAEs or AEs, even if it is not directly related to the study, the researchers must report it to the research team within 24 hours and stop the trial. If a serious programming error occurs with the AI system or if significant problems are found in user interactions, the researchers must stop the trial right away. The team will fix the technology and improve the user interface of the AI system. After the problem is fixed and checked again, the study can be redesigned and restarted to ensure the participants are safe and the research is valid.

Before the study starts, experts will organize training sessions and evaluations to ensure all team members understand the procedures and technical details. To reduce the risk of missing follow-up, we will keep a list of all participants and assign each one a unique identification code. Also, to ensure both the intervention and control groups are consistent, all survey times will be the same, and the same validated questionnaires will be used. To make sure the data is accurate, we will use a double data entry and checking process, which will improve data quality. We will also talk to statistical experts regularly to choose the best methods for the study. During data processing, if we find any abnormal data, we will check the original questionnaires to make sure the data is correct. Only after confirming that the data is fully accurate will we use it for the final analysis.

The principal investigators will regularly check the work of the research team to make sure the study protocol is followed and the data is collected properly. If the team does not follow the survey and follow-up procedures, the investigators may take action, such as stopping the trial or changing the randomization plan. After these changes, data collection will start again. If there are problems with the questionnaire design or mistakes in recording data, the team will stop the trial, fix the issues, and redesign the questionnaire. After making the changes, the updated questionnaire will be given to participants to ensure the data matches the study’s goals and expected results. This will help keep the study’s science and data reliable, ensuring the results are valid. The data will be managed by a data administrator. The trial manager will oversee data recording and handle any problems with cloud storage, data management, and access. The trial manager will also check regularly to ensure the data is accurate, reliable, and follows the study protocol.

This study allowed unblinding in special situations. These situations include urgent medical needs, such as when a participant has a serious adverse event or needs urgent treatment where knowing the group assignment is important. Unblinding can also happen for valid medical reasons by the participant or their healthcare provider after the study ends. The unblinding process starts with a written request from the principal investigator or a member of the clinical oversight team. The Clinical Review Panel will review all unblinding requests to decide if the conditions are met. If approved, the study team will securely reveal the group assignments following a set protocol.

All proposed changes to the study will first be discussed by the steering committee. After agreeing, the changes will be sent to the hospital’s ethics committee and the research department for approval. Once approved, an official document with the changes will be given to all relevant parties, and an electronic copy will be available if needed. Any changes from the protocol will be recorded by the trial leader and signed by the principal investigator. This document will be kept with the other trial records. After getting approval from the steering committee, research department, and ethics committee, the trial leader will update the clinical trial application.

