### Study sample

2.3

This research will adopt a continuous enrollment method to recruit families of children diagnosed with asthma from April 2025 to December 2026. The detailed inclusion and exclusion criteria are as follows:

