#### Withdrawal criteria

2.3.3

Voluntary withdrawal: Families have the option to withdraw from the study for personal reasons. For example, they might face scheduling conflicts that prevent them from devoting the necessary time to the study, or their interest in participating may wane over time.Severe adverse events: Participants who encounter serious adverse events, such as severe physical illnesses or acute incidents like a heart attack or severe infection, which necessitate the interruption of the intervention, will be removed from the study.Changes in treatment: If a participant’s condition changes, or they receive medical advice to alter their treatment plan in a way that conflicts with the study intervention, they will be excluded.

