### Sample size

2.4

Given that this study is a pilot RCT, its primary focus is on evaluating the feasibility and practical implementation of the AI-HEALS intervention. Therefore, it is not designed to perform statistical hypothesis testing but rather to collect preliminary data on intervention operability and acceptability. As such, the sample size estimation for this pilot RCT does not follow traditional power analysis methods used for hypothesis testing. Instead, a pragmatic rule of thumb was applied to select a sample size sufficient to determine outcome variability and identify any operational issues (27). In line with the suggestions put forward by Billingham et al., the sample size for this pilot study is set at around 25 participants per group, amounting to a total of 50 participants (27). Anticipating an attrition rate of 20%, we determined that a minimum total sample of 60 participants (30 per group) would be necessary.

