#### Control group: standard treatment group

2.7.1

Participants assigned to the control group will receive standard medical care delivered by a multidisciplinary clinical team. This care includes: 1) regular physician consultations for health assessment and treatment plan adjustments; 2) scheduled follow-up visits at predefined intervals to monitor disease progression; 3) comprehensive diagnostic evaluations to track health indicators; 4) structured health education sessions focusing on condition management, treatment adherence, and lifestyle modifications; and 5) evidence-based referrals to specialized care providers when clinically indicated. This integrated approach ensures alignment with clinical practice guidelines while maintaining ethical research standards and routine asthma management protocols.

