### Variables measurement

2.10

At the baseline stage, sociodemographic variables will be collected. Physical examinations and questionnaires are scheduled to be completed at the baseline, upon discharge, and at the end of the intervention (**Table 1**).

Sociodemographic Variables: A custom-designed demographic questionnaire will be utilized to measure the following variables: the child’s gender and age, the ages of the parents, marital status, type of household registration, number of persons in the household, education level, occupation, income status, as well as the child’s asthma symptoms and a detailed medical history.Anthropometric Variables: Each participant’s height, weight, waist circumference, and blood pressure will be measured twice, using certified instruments to ensure accuracy. Height and weight measurements will be carried out using fully calibrated, certified electronic devices. The BMI will be calculated by dividing the weight in kilograms by the square of the height in meters. To measure the waist circumference, a measuring tape will be used at the level of the navel.Pulmonary Function Tests: The MasterScreen series pulmonary function testing system from Jaeger (Germany) will be used to conduct pulmonary function tests. Key indicators include the Forced Expiratory Volume in 1 second (FEV_1_), Forced Vital Capacity (FVC), the FEV_1_/FVC ratio, Peak Expiratory Flow (PEF), and the forced expiratory flow at 25%, 50%, and 75% of FVC exhaled (FEF_25_%, FEF_50_%, FEF_75_%) (30).

**Table 1 T1:** The schedule of enrolment, interventions, and assessments.

Study period	Recruitment	Intervention	
Timepoint	0	Discharge	3 Months
Eligibility screen	✓		
Informed consent	✓		
Allocation	✓		
Sociodemographic variables	✓		
C-ACT	✓	✓	✓
PFT	✓	✓	✓
s-EMBU-C	✓	✓	✓
PHQ4	✓	✓	✓
PSSS-SF	✓	✓	✓
NGSES-SF	✓	✓	✓
EQ-5D-5L	✓		✓
Smoking	✓		✓
Alcohol consumption	✓		✓
B-PSQI	✓		✓
FCS-SF	✓		
eHEALS	✓		

B-PSQI, The new Brief Version of the Pittsburgh Sleep Quality Index-Short Form; C-ACT, Childhood Asthma Control Test; eHEALS, The eHealth Literacy Scale; FCS-SF, The Family Communication Scale-Short Form; EQ-5D-5L, EuroQol-5 Dimensions 5 Levels; PFT, Pulmonary Function Tests; PHQ-4, the abbreviated Patient Health Questionnaire-4; PSSS-SF, The Perceived Social Support Scale; NGSES-SF, The New General Self-Efficacy Scale-Short Form; s-EMBU-C, Short-Form Egna Minnen av Barndoms Uppfostran for Chinese.

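### The adverse-event rule in Study management stops the whole trial for any event in any child, and conflicts with the protocol's own withdrawal criteria

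*Protocol article*

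**What the plan says.** The protocol article gives three instructions that bear on this point.

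- **Adverse events, section 3 (Study management).** The trigger is any SAE or AE in a participant, including one with no direct link to the study. The action is that "the researchers must report it to the research team within 24 hours and stop the trial".
- **Serious adverse events, section 2.3.3 (Withdrawal criteria).** Participants who have serious events "which necessitate the interruption of the intervention, will be removed from the study". The unit is the participant, and the trial is not said to stop.
- **AI faults, section 3, directly after the adverse-event rule.** After a serious programming error, or "if significant problems are found in user interactions, the researchers must stop the trial right away". The technology is then repaired, and "After the problem is fixed and checked again, the study can be redesigned and restarted".

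Section 3 also lets the DMC suspend or terminate the study. The grounds it names are departures from the approved protocol and unauthorised changes; safety events are not among them. A later part of section 3 provides for unblinding a participant's allocation after a serious event, on written request and after review by a panel.

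**The concern.** The two adverse-event instructions cannot both be followed. Under section 2.3.3, a serious event ends one child's participation if the intervention has to be interrupted, and a non-serious event ends nobody's. Under section 3, either kind of event, related or not, stops the trial. Staff facing a child with a mild unrelated infection cannot tell whether to file a report, interrupt one family's intervention, or halt recruitment, intervention and assessments for everyone.

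At stake is whether the pilot can finish. The rule has no severity threshold and no relatedness condition, so its trigger is close to routine in a group of children followed for three months after a hospital admission for asthma. The sample was meant to "select a sample size sufficient to determine outcome variability and identify any operational issues". Repeated whole-study stops for unrelated minor events would work against both of those aims and would add no safety for the other families.

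The AI-fault sentence has a milder form of the same looseness, because it does not say what happens to scheduled assessments during the pause. The control arm does not use the system: "Participants assigned to the control group will receive standard medical care delivered by a multidisciplinary clinical team".

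**Working it through.** **1. Is there a limit anywhere on the adverse-event stop?** The sections on randomisation and blinding, withdrawal, consent, interventions, adherence and study management contain no sentence that restricts it to one participant, one arm or serious events. Section 2.3.3 is the only participant-level rule, and it differs in three respects:

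| | Section 3 | Section 2.3.3 |
|---|---|---|
| Trigger | any AE or SAE | serious event only |
| Condition | none; unrelated events count | the intervention has to be interrupted |
| Unit affected | the trial | the participant |

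**2. How often would the literal rule be triggered?** The protocol gives no adverse-event rate, so there is no stated figure to reproduce. Input: n = 60 (section 2.4). Assumptions: a probability p that a child has any AE during follow-up, and independence between children. The chance of at least one trigger is 1 − (1 − p)^60.

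- p = 1%: 1 − 0.99^60 = 0.453
- p = 5%: 1 − 0.95^60 = 0.954
- p = 10%: 1 − 0.90^60 = 0.998

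The expected number of children with an event is 60p, that is 0.6, 3 and 6. At 5% or more the rule would almost certainly be invoked, and probably more than once.

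**3. What could the AI-fault stop cost?** The documents give no probability of a fault, so everything here is conditional on a stop. Recruitment is described thus: "This research will adopt a continuous enrollment method to recruit families of children diagnosed with asthma from April 2025 to December 2026". Assessments are set as follows: "Physical examinations and questionnaires are scheduled to be completed at the baseline, upon discharge, and at the end of the intervention". Assume even accrual of 60 families over A months, with A = 21 (April 2025 to December 2026) or A = 18 (the same window less three months for the last follow-up).

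- Accrual rate: 60/18 = 3.33 or 60/21 = 2.86 families per month.
- Families between allocation and the 3-month visit, from month 3 until accrual ends: 3 × rate = 10.0 or 8.6 (16.7% or 14.3% of 60). About half, 5.0 or 4.3, are controls.
- Evaluable with the planned 20% attrition and no stop: 60 × 0.8 = 48.
- For a pause of d months in which assessments are not done, not made up and not replaced: evaluable = (60 − rate × d) × 0.8, and interval-width ratio = √(48/evaluable). The loss is capped at d = 3, when every mid-course family has been missed.

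| Pause | Evaluable (A = 18; 21) | Width ratio (A = 18; 21) |
|---|---|---|
| 1 month | 45.3; 45.7 | 1.029; 1.025 |
| 2 months | 42.7; 43.4 | 1.061; 1.051 |
| 3 months or more | 40.0; 41.1 | 1.095; 1.080 |

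If assessments continue during the pause, the loss is zero.

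**The case against.** The strongest reply on adverse events is that the wording is merely loose. The sentence speaks of a participant, section 2.3.3 removes individuals, the unblinding provision handles serious events one at a time, and the DMC has separate power over the whole study. All of this makes best sense if the trial carries on after one child's event. That is probably what was meant, and the 45% to 99.8% figures describe only the literal reading at assumed rates. But section 3 does not say so. An instruction about adverse events has to be usable as written, so the likely intent supports the correction and does not remove the need for it.

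On AI faults the reply is stronger. The trigger is a serious error or significant problems in a system that advises parents of children with asthma. Pausing to repair it is a sound safety choice and a defensible validity choice, since a comparison collected meanwhile would partly test a broken or superseded version. Fixing and restarting also suits a pilot looking for operational problems.

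A reader might infer from the words about redesign and restart that follow-up ends, that data already collected are dropped, or that control families are needlessly cut off. The documents do not support that. Section 3 never says that assessments stop or that data are discarded. Section 2.12 sets an intention-to-treat analysis with multiple imputation, and section 3 also provides for a participant list to limit loss to follow-up and for approval and recording of changes. What remains is a wish for one clarifying sentence.

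**Conclusion.** The adverse-event rule is wrong as written. It is unlimited in scope, takes in minor and unrelated events, and contradicts section 2.3.3. Followed literally, it would stop a 60-family trial with probability 45%, 95% or 99.8% at assumed per-child risks of 1%, 5% or 10%, taking events as independent between children. No sample size or analysis figure in the protocol changes; what is exposed is the trial's ability to run to completion and the staff's ability to act consistently.

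The AI-fault rule is a minor secondary point. Its immediate stop may stand. Any loss of precision depends on a stop of unknown probability and on assessments lapsing without being made up. It ranges from nothing to intervals about 8% to 10% wider after a pause of three months or more, under even accrual over 18 to 21 months. The study describes itself as a pilot not designed for hypothesis testing, so this is modest.

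**What to change.** **Adverse events.** Reword the action in section 3 to: *report within 24 hours and, where the event requires it, interrupt that participant's AI-HEALS intervention*. For a control child this means reporting only. Keep the family on the Table 1 assessments where possible and in the intention-to-treat analysis, and align section 2.3.3 so that removal means the intervention ends, not the assessments.

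**Whole-study suspension.** Reserve it for the DMC and the Ethics Committee, and add safety events to the DMC's stated grounds. Without that addition, the DMC would have no stated authority to act on them.

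**AI faults (minor).** Keep the immediate suspension of AI-HEALS, and of new enrolment if needed. Add that scheduled assessments of families already randomised continue in both arms during the pause, and log the dates of the fault and the system version as an operability result.

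**Cost.** A short wording amendment through the existing approval route, plus a fault log. The safety response to an individual child's event or to a faulty system is not weakened. The one real downside lies with AI faults: some intervention families will have had reduced exposure, up to one third of a 3-month course for a 1-month pause and two thirds for a 2-month pause. This dilutes the contrast and should be reported with the result.

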Children’s Asthma Knowledge-Based Intelligent Question-Answering System (KBQA): This program aims to help parents of asthmatic children better understand asthma. It plays a role through the FAQ robot (FAQrobot), so that families can efficiently and accurately obtain the knowledge related to childhood asthma. In order to achieve this goal, we will develop a thorough and accurate knowledge base around childhood asthma. The knowledge base will cover a wide range of aspects, including the basic concepts of disease, etiology, symptoms, treatment methods, drug use, daily management, appropriate diet and appropriate sports activities. We will integrate this knowledge base into the large language model of Doubao (developed by ByteDance). In this way, the model can learn from the database and provide professional answers to patients’ questions directly on the WeChat platform. In addition, in order to enhance the interaction and user participation, the system will ask three related questions each time the user queries. This encourages users to explore further and interact more deeply with the system. In order to continuously optimize the knowledge base and better meet the needs of users, we will record the query and usage behavior of participants at the back end of the system, such as the time and frequency of accessing the system. By analyzing this data, we can identify the patterns of participants’ behavior. Based on these insights, we will be able to adjust and improve the knowledge base and question-and-answer system to ensure that the information is up-to-date and accurate. In the whole question-and-answer interaction process, the system supports text and voice input. This greatly reduces the threshold for users operating the system, so that more people can access the system.Recording and Monitoring of Physiological Indicators and Lifestyle Changes: In this study, the AI-HEALS will be used to encourage childhood asthma families to regularly record lifestyle factors, including weekly medication adherence, dietary habits, and physical exercise. Participants can directly input data into the system, allowing researchers to review recorded content in real-time through a backend interface, enabling long-term tracking and monitoring of self-management behaviors. To ensure data relevance and accuracy, the research team will jointly develop SMART (Specific, Measurable, Achievable, Relevant, Time-bound) plans with families during the initial phase of engagement. Data collection processes will be structured around these plans, with system-generated reminders sent every Saturday prompting detailed information uploads. This approach allows comprehensive assessment of intervention impacts on patients’ daily lives while ensuring data alignment with family-specific goals.Customized Reminder Services: In order to improve treatment compliance, the AI-HEALS system will provide a personalized reminder service. Participants can flexibly set reminders for various important tasks, such as medication and exercise. Once these reminders are set, the system will automatically send notifications at the specified time. This reminder service is designed to help patients strictly abide by medical advice, promote the long-term sustainability of healthy behaviors, and ultimately help to better control asthma.Automated and Personalized Asthma Science Articles for Family: The system will also run a mechanism to automatically distribute educational articles. Every week, families of children with asthma will automatically receive one to three articles on asthma management. These articles will cover a variety of topics. It includes dietary recommendations, such as which foods are good for asthmatic children and which foods should be avoided. Sports suggestions will also be provided to guide children to carry out sports activities of the appropriate type and intensity. It will also provide information on the correct medication, such as the correct method of medication and potential side effects that should be paid attention to. According to the interactions between the family and the system, such as the types of questions they raised, the frequency of visits, and the topics they are more interested in, targeted educational articles will be pushed accurately to meet the unique needs of each family. In order to maximize the effectiveness of information dissemination, the research team will regularly review the background data. This includes analyzing the number of articles that the participants visited, the different types of articles they liked, and the length of time they spent reading each article. According to this data, the article content and dissemination frequency will be adjusted.

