#### Primary outcomes

2.9.1

The primary outcome was changes in asthma symptom control, measured using the Childhood Asthma Control Test (C-ACT) at baseline, discharge, and post-intervention. Given the nested longitudinal structure of repeated measurements within families, we employed multilevel negative binomial models to analyze asthma symptom frequency (count data), estimating incidence rate ratios (IRRs) and 95% confidence intervals (CIs).

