
### Statistical analysis

2.12

This study will collect quantitative data through questionnaires and process the data using Microsoft Excel. Data analysis will follow the intention-to-treat principle. For continuous variables, descriptive statistics will show means ± standard deviations or medians and interquartile ranges (P25, P75), depending on the data. Normally distributed continuous variables will be compared using the Student’s t-test or one-way analysis of variance (ANOVA). Non-normally distributed data will be analyzed with non-parametric tests. The normality of the data will be checked using the Kolmogorov-Smirnov test. Categorical variables will be shown as sample percentages (n) and analyzed using the Chi-square test. For missing data, multiple imputation using chained equations (MICE) will be used, with 50 iterations to ensure convergence. The imputation method will be predictive mean matching (PMM), with 5 neighbors and 20 imputed datasets.

In the cross-sectional data analysis, this study will use linear regression, logistic regression, and structural equation modeling (SEM) to examine the relationships between behavioral patterns and mobile health applications. Given the nested structure of parent-child dyads within families, we employed multilevel models with family-level random intercepts to account for within-family correlations. For child health outcomes (asthma-related events and symptoms), a two-level negative binomial model was utilized to estimate IRRs and 95% CIs, adjusting for family-level variables (parents’ parenting styles, household income, marital status) and child-level variables (age, sex). For parental outcomes (continuous data), a two-level linear mixed model was applied to evaluate intervention effects, adjusting for family-level variables (marital status, household income) and parent-level variables (age, education, parents’ parenting styles). *Post hoc* comparisons of estimated marginal means were conducted using the emmeans package to test between-group differences. Model fit was validated through convergence checks, residual analysis, and overdispersion testing for count data. All analyses were performed in R (version 4.3.1; R Foundation for Statistical Computing, Vienna, Austria) using the lme4 package (version 1.1-33). An independent statistician with no conflicts of interest conducted the analysis. All statistical tests were two-tailed, with a significance level of 0.05.

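### Section 3 leaves the choice of methods open although section 2.12 fixes them, and 2.12 does not rank its two analysis tracks; reporting the more favourable one would raise the per-outcome error rate from 5% to about 6–8%

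*Protocol article*

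**What the plan says.** Section 3 (Study management), in a paragraph on training, follow-up lists, double entry and data checking, says: "We will also talk to statistical experts regularly to choose the best methods for the study". It gives no end date and does not tie the consultation to a stage before data are available.

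Section 2.12 (Statistical analysis) already fixes methods, down to imputation settings and software versions. It contains two tracks:

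- **Simple tests.** Continuous variables judged normal by a Kolmogorov-Smirnov test go to a t-test or ANOVA. Otherwise, "Non-normally distributed data will be analyzed with non-parametric tests". Categorical variables go to a chi-square test.
- **Adjusted models.** "For parental outcomes (continuous data), a two-level linear mixed model was applied to evaluate intervention effects". For child asthma events and symptoms, "a two-level negative binomial model was utilized to estimate IRRs and 95% CIs". Each model has five named covariates.

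On the error rate, the section says "All statistical tests were two-tailed, with a significance level of 0.05".

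Section 2.9.1 defines the primary outcome as change in C-ACT, measured three times. The model sentence that follows concerns a different quantity: "we employed multilevel negative binomial models to analyze asthma symptom frequency (count data"). Section 2.11 describes the C-ACT as a total score from 0 to 27.

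**The concern.** Two statements about the methods cannot both govern. Either 2.12 fixes them, or they are still to be chosen in recurring consultations. If a separate analysis plan exists and fixes them, the section 3 sentence conflicts with that plan too.

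The second gap lies inside 2.12. A continuous parental outcome falls under both tracks, and the text does not say which result counts if they disagree. The C-ACT is worse placed. As a score it fits the simple track, while the model placed beside it is for counts of symptoms, so the deciding primary analysis cannot be identified from the article.

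A 5% test and its 95% interval keep their stated meaning only if the analysis was fixed without regard to its result. With two unranked tracks and an open invitation to choose methods, a reader of the final report could not tell whether that condition held.

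**Working it through.** **1. The plan's own figure.** For one pre-named two-sided test at 0.05, the error rate is 1 − (1 − 0.05)¹ = 0.05. This reproduces the level in 2.12. The article states no power and no family-wise rate.

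**2. The tracks side by side.**

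| Outcome | Simple track (2.12) | Model track (2.9.1, 2.12) | Ranking stated |
|---|---|---|---|
| C-ACT score, 0–27 (primary) | t-test or rank test, chosen by normality test | only a negative binomial model for symptom frequency | none |
| Parental continuous outcomes | the same | adjusted two-level linear mixed model | none |
| Child asthma events and symptoms | covered only by the general wording | adjusted two-level negative binomial model | none |

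**3. Bounds for reporting the better of two valid 5% tests under no effect.**

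- Upper bound, whatever the dependence: 2 × 0.05 = 10%.
- Independent tests: 1 − 0.95² = 9.75%.
- Correlated test statistics: 1 − P(|Z₁| ≤ 1.96 and |Z₂| ≤ 1.96), bivariate normal.

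| Correlation | 0.5 | 0.7 | 0.8 | 0.9 | 0.95 | 0.99 |
|---|---|---|---|---|---|---|
| Either significant | 9.1% | 8.4% | 7.8% | 7.0% | 6.5% | 5.7% |

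An unadjusted and an adjusted analysis of the same outcome are strongly correlated, so the right-hand part of the table is the relevant one.

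**4. Null simulations of the continuous tracks.** From the article come 25 per arm analysed and 30 per arm enrolled (section 2.4), 1:1 allocation (2.2), two-sided 0.05 and five covariates per model (2.12). Outcome distributions and correlations are assumptions, since the article gives none.

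- The two written tracks, five covariates, 25–30 per arm: 6.4–7.9%.
- t-test or a model adjusted for the baseline score and further covariates, 25 and 30 per arm, 8,000 runs per setting, baseline–outcome correlation 0.3 to 0.7: 6.9–8.2%. Each test alone ran at 4.4–5.4%. The Monte Carlo standard error near 7% is √(0.07 × 0.93 / 8,000) = 0.0029, or about 0.3 percentage points.
- t-test or adjusted model with six covariates, 24 and 30 per arm, normal and log-normal outcomes, 6,000 runs per setting: 5.8–6.9%.

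Together these give about 6–8%, which matches correlations of roughly 0.8 to 0.95 in the table above.

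**5. Count outcomes, for comparison.** With 25 per arm, about 1,200 runs per setting, assumed means of 3–5 and dispersions of 0.5–1.5, a t-test or an unadjusted single-level negative binomial test gave 5.8–7.0%. A rank test or the same model gave 7.3–7.8%. Pairing either simple test with the adjusted negative binomial model gave 8.5–9.8%, but that model alone already ran at 7.7–8.3% at this size. Most of that excess is therefore small-sample error in the model, not an effect of choosing.

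**6. After the fix.** With one analysis per outcome, named in advance, the nominal rate returns to 5% for that outcome, provided the named test is itself valid at this size.

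**The case against.** The strongest reply has five parts.

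- **The sentence is vague.** It stands in a data-quality paragraph that opens with activities before the study, and it does not say that methods will be chosen after results are seen. That stands: a reader might infer repeated re-choosing in the light of the data, but the article does not state it. What remains is an open-ended choice beside methods already fixed.
- **Safeguards exist.** Section 2.2 keeps analysts blinded, and section 3 sends changes through the steering committee and then the ethics committee and research department. Both count. Neither closes the gap. Two-sided p-values can be compared without arm labels, the amendment route sets no cut-off relative to outcome data, and picking between two methods already listed may not count as a change.
- **Models are assigned.** Section 2.12 ties the mixed model to intervention effects, and the simple tests stand beside the descriptive statistics. One can read the models as the main analysis, so it would be too strong to say that no analysis is assigned. The ranking is still unstated, and the reading does not help the C-ACT score.
- **This is a pilot.** Section 2.4 disclaims hypothesis testing, which limits the weight of any error-rate figure. Section 2.12 nevertheless tests at 0.05, and the Discussion makes improvement in C-ACT the main purpose.
- **A separate analysis plan may settle the choice.** It may, and a freeze date could properly be left to it. The section 3 sentence would then need to defer to it.

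Two further inferences fail. The system backend, "allowing researchers to review recorded content in real-time through a backend interface", shows the intervention arm's medication, diet and exercise entries. It is not said to show C-ACT or any control data, so it does not reveal a between-arm result. Nor do the planned imputations force the two tracks onto different data: chi-square and rank results can be combined across imputed datasets, and the article does not say otherwise.

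**Conclusion.** The point holds as a conflict of wording and a missing ranking. Section 3 leaves open what section 2.12 fixes. Section 2.12 does not place its models above its simple tests, and the C-ACT score has no fitting model named.

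The size is modest: about 6–8% per continuous outcome instead of 5% if the more favourable of the two written tracks is reported, with a ceiling of 10% for two valid tests. This rests on assumed outcome distributions and correlations, and on the result guiding the choice. If the choice does not follow the result, there is no rise from this source.

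A reader might infer rates of 12–13%. Simulations reach that range only by adding baseline-adjusted and change-score analyses and taking the best of six. The article does not list those as rival analyses, so the higher figure should not be attributed to the plan. The matter should be corrected, and wording is enough.

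**What to change.** 1. **Section 3.** Delete the sentence on choosing methods, or limit it to consultation before outcome data by arm are available. State that any later change of method goes only through the amendment route already in section 3, and is decided by people who have not seen outcome data by arm.
2. **Section 2.12, with 2.9.1.** Name one deciding analysis per outcome. For C-ACT, use a model for a continuous score at 3 months with the stated covariates, and say how the baseline score enters, because the outcome is defined as a change. For parental outcomes, use the adjusted linear mixed model. Keep the count model for symptom counts.
3. **Section 2.12.** Label the t, rank and chi-square tests as descriptive or supportive.

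The cost is protocol wording and the loss of later flexibility in methods. No extra participants, visits or measurements are needed.
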